## Abstract

**Background:**

Obesity is a persistent public health concern and a risk factor for many chronic diseases including at least 13 different cancers. Adult Black females have the highest prevalence of obesity (57%) compared to other racial/gender groups in the U.S. Although behavioral weight loss (BWL) interventions have demonstrated effectiveness, Black females tend to lose less weight than White counterparts. The higher prevalence of chronic psychological stress reported by Black females may contribute to their disproportionate prevalence of obesity and observed suboptimal weight loss. This study will examine the effectiveness of a 12-month culturally-targeted, stress management-enhanced BWL intervention on weight loss and stress reduction among Black females in a fully-powered randomized, controlled trial.

**Methods:**

Adult Black females with obesity (*n* = 340) will be randomized to either a culturally targeted stress management-enhanced BWL intervention (BWL-Stress) or the same BWL intervention alone (BWL-alone). The primary outcome is weight change at month 6. Secondary outcomes will include changes in stress measures (e.g., perceived stress, cortisol), energy intake, and physical activity at month 6. We will also assess process measures (e.g., treatment adherence, treatment burden). Each outcome will also be evaluated at month 12 to assess longer-term effects of the intervention.

**Discussion:**

This novel approach for enhancing an evidence-based BWL program with culturally-targeted stress management strategies for Black females addresses an understudied barrier to effective weight management among a population at high risk for obesity and obesity-related chronic diseases. This study will potentially elucidate psychological or behavioral mechanisms linking our novel intervention to study outcomes. If the intervention is proven to be effective, this study will have significant clinical and public health implications for weight management among Black females.

**Trial registration:**

This study was registered on ClinicalTrials.gov, identifier NCT04335799t, on April 6, 2020.

## Background

In the US, Black adults are disproportionately affected by cancer, with the highest death rate of any racial or ethnic group [1]. The lifetime risk of cancer for Black adults is 1 in 3, and more cases occur among females than males [2]. Nearly 40% of US adults have obesity, a risk factor for 13 types of cancer [3]. The highest prevalence of obesity is among Black females, at approximately 57% [4]. Given that obesity is a strong risk factor for cancer [5], effective strategies for weight management are needed to combat the obesity epidemic and the resulting risk for several types of cancer and other chronic conditions, especially in those at highest risk.

Although behavioral weight loss (BWL) interventions have been effective at promoting weight loss in some individuals with obesity, these programs still result in less weight loss among Black females compared to White counterparts [6, 7]. Even the Diabetes Prevention Program (DPP) Intensive Lifestyle Intervention, which produced clinically meaningful weight loss (3-5% of baseline weight) among Black women (4.7 kg weight loss at 6 months), achieved 2.8 kg greater weight loss in White women and significantly greater weight loss among all race-gender groups (*p* < 0.01) except for Black men, indicating a need to examine sociocultural and environmental factors for successful BWL interventions among Black women [8]. Disparities in weight loss outcomes of Black and White individuals have also been reported in several other BWL trials [9]. To improve weight loss outcomes among Black women, research on culturally-adapted interventions and mechanistic links between cultural factors and weight loss is warranted [10].

Psychological stress is associated with weight gain over time and higher body mass index (BMI) [11–13]. In previous BWL interventions, individuals with higher stress at the start of the weight loss program went on to lose less weight than those with lower stress [14, 15]. Given that Black females report higher chronic stress than other groups [16], have a unique stress experience due to the intersection of race and sex [17], and tend to employ coping strategies that may be detrimental to health [18–22], the role of stress on weight control efforts may be particularly relevant for Black women. There is a well-established literature on stress reduction interventions that address racial/ethnic, health, and socioeconomic differences in stress exposure and stress-related outcomes [16], as well as observational relationships suggesting that high stress levels may contribute to enduring and increasing adiposity [11]. However, there remains a gap in the literature about whether adding a culturally-targeted stress management component to an evidence-based BWL intervention will produce greater weight loss than the standard intervention. A 2018 review [13] reported that only two small studies have investigated how adding stress management training to BWL programs affects weight loss: one reported significant positive effects among Greek women [23], and the other, conducted in a sample of Black women, reported encouraging trends but was underpowered to detect significance [24]. In addition, a randomized BWL program that tested the addition of mindfulness training for stress reduction in a predominantly (60%) White sample did not lead to greater weight loss, although it led to greater glucose control, a secondary outcome [25]. The participants of color attended fewer sessions in the mindfulness condition, and had less weight loss, again suggesting culturally tailored stress reduction is needed [26]. The purpose of this study is to examine whether a culturally-targeted, stress management-enhanced BWL intervention will improve weight loss and stress reduction among Black females in a fully powered randomized, controlled trial.

### Aims and hypotheses

This study examines whether a culturally-targeted, stress management-enhanced BWL intervention (BWL-Stress) is effective in reducing weight compared to a standard BWL intervention (BWL-Alone) among adult Black females with obesity and elevated stress levels. The primary aim is to conduct a randomized controlled trial to determine the effects of BWL-Stress on body weight compared to BWL-Alone among adult Black females with obesity and elevated perceived stress. Black women with co-existing obesity and elevated stress as measured by a validated survey will be randomized to BWL-Stress or BWL-Alone. We hypothesize that BWL-Stress will lead to greater weight loss at 6 months than BWL-Alone. The second aim is to evaluate the effects of BWL-Stress on multidimensional stress as measured by a validated survey instrument and a stress biomarker. Perceived psychological stress will be measured by the Perceived Stress Scale (PSS-10) [27] and the Stress and Adversity Inventory (STRAIN) [28], and salivary cortisol (assessing the cortisol awakening response) will be collected as an objective measure of stress at baseline and multiple follow-up time points to be able to compare changes by intervention group over time. We hypothesize that BWL-Stress will lead to greater reduction in perceived stress and more improvement in cortisol level at 6 months than BWL-Alone. The third aim is to determine whether the relationship between BWL-Stress and weight change is mediated by perceived stress, energy intake, and/or physical activity. A multiple mediation model will be used to determine if perceived stress level, energy intake, and/or energy expenditure explain observed relationships between the stress management-augmented intervention and weight change. We hypothesize that the relationship between BWL-Stress and 6-month weight change will be partially mediated by PSS-10 score, energy intake, and physical activity.

## Methods/design

Participants (*n* = 340) will be randomized to one of two treatment conditions: BWL-Stress or BWL-Alone. Both groups will receive the same evidence-based BWL program over 26 sessions. In addition to the BWL program, the BWL-Stress group will receive training on stress management, whereas the BWL-Alone group will receive education on general women’s health topics as an equivalent attention control. Participants will meet for group-based sessions weekly for 4 months, bi-weekly for 2 months, and then monthly for 6 months.

### Participants

Black females aged 21-75 years with a BMI of at least 30 kg/m^2^ and elevated stress levels (PSS-10 score ≥ 13) will be eligible for inclusion. Individuals will be excluded if they: 1) are pregnant or are planning to become pregnant in the next year, 2) have a known major medical or psychological condition known to influence body weight (e.g., medicated or poorly controlled diabetes [fasting blood glucose > 126 mg/dL], cardiovascular event in the preceding 12 months, history of gastric bypass surgery, bariatric surgery, or eating disorder), 3) history of psychiatric hospitalization in past 2 years, 4) history of substance abuse or eating disorder, or 5) any condition for which a medical professional has suggested diet modification, physical activity, and/or weight reduction would be contraindicated.

### Sample size and power

While primary analysis will be adjusted for prognostic factors for weight loss, sample size was determined using an equal variance t-test. Preliminary data identified a 1.4 kg loss for Lifestyle alone and 2.7 kg loss for Lifestyle + Stress interventions, with standard deviations of 2.1 and 4.0 kg, respectively, yielding a Cohen’s d of 0.44 [24]. As these measures were taken at 3 months, and the current study is assessing 6-month weight loss, larger effects are likely; however, to reduce the likelihood of using an effect size which is too large [29], the study has been powered for a Cohen’s d of 0.35. This effect comes from assuming the above with both groups having a 4 kg standard deviation. Thus, with 85% power and a Type 1 error rate of 0.05, 148 participants are needed per group for a total of 296 participants. To allow for 10% attrition without loss of power, 340 participants (170 per group) will be enrolled and randomized.

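### The planning effect of d = 0.35 does not follow from the inputs given as its source (1.3/4 = 0.325); if the printed pilot means are right, power is about 80% rather than 85%

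*Protocol article*

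**What the plan says.** All the relevant statements are in the Sample size and power section of the protocol article.

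- Test: "sample size was determined using an equal variance t-test".
- Pilot means: "Preliminary data identified a 1.4 kg loss for Lifestyle alone and 2.7 kg loss for Lifestyle + Stress interventions". The pilot SDs follow, "with standard deviations of 2.1 and 4.0 kg, respectively", together with a pilot Cohen's d of 0.44.
- Planning effect: "the study has been powered for a Cohen’s d of 0.35". It is presented as a guard against assuming too large an effect, and its origin is given as "This effect comes from assuming the above with both groups having a 4 kg standard deviation".
- Resulting size: "with 85% power and a Type 1 error rate of 0.05", "148 participants are needed per group for a total of 296 participants".
- Enrolment: "To allow for 10% attrition without loss of power, 340 participants (170 per group) will be enrolled and randomized".

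**The concern.** The section names the source of its planning effect, and that source gives a smaller number. The reader is told to take the pilot means, set both SDs to 4 kg and arrive at 0.35. Doing so gives 0.325.

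This paragraph is the only power justification for the primary comparison. A reader of a null result would take it that the trial had 85% power to detect the pilot difference of 1.3 kg. On the printed means, the chance of missing that difference is about 20%, not 15%, and the allowance for attrition without loss of power does not hold for that difference.

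**Working it through.** **Inputs** (all from the Sample size and power section): mean losses 1.4 and 2.7 kg; pilot SDs 2.1 and 4.0 kg; planning SD 4 kg in both groups; planning d 0.35; power 85%; type 1 error 0.05; 148 per group; 10% attrition; 340 randomised. Sidedness is not stated. Power figures below use the noncentral t distribution, 1:1 allocation.

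**Step 1: reproduce the plan's own figure.** For d = 0.35, 85% power and two-sided 0.05, the t-test needs 147.6 per group, so 148. Power at 148 is 85.1%. A one-sided test would need 118 (normal approximation), which does not match. The step from d to N is therefore correct and two-sided.

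**Step 2: derive d from its stated source.**
- d = (2.7 − 1.4)/4 = 1.3/4 = 0.325.
- Difference needed for d = 0.35 at SD 4 kg: 0.35 × 4 = 1.4 kg.
- SD needed for d = 0.35 at 1.3 kg: 1.3/0.35 = 3.71 kg.

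Neither 1.4 kg as a between-group difference nor 3.71 kg as an SD is stated as an assumption.

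**Step 3: consequence if the printed means are right (d = 0.325).**

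| Evaluable per group | Power at d = 0.325 | Power at d = 0.35 |
|---|---|---|
| 148 (stated need) | 79.6% | 85.1% |
| 153 (170 × 0.9) | 80.9% | 86.2% |
| 170 (no attrition) | 84.8% | 89.6% |

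For 85% power at d = 0.325 the test needs 171.0 per group by calculation, that is 171, or 342 evaluable. Allowing for 10% attrition, 342/0.9 = 380 randomised.

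**Step 4: can rounding explain it?** Rounding 0.325 to two decimals gives at most 0.33, with 80.8% power at 148 per group. If the means themselves were rounded, the true difference lies between about 1.2 and 1.4 kg. Only the extreme upper end gives 1.4/4 = 0.35. The lower end gives 1.2/4 = 0.30 and 73% power at 148 per group.

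**Step 5: check the other effect size in the section.** Assuming equal pilot groups (their sizes are not given), the pooled SD is √((2.1² + 4.0²)/2) = √10.205 = 3.19 kg.
- 1.3/3.19 = 0.41, not the printed 0.44.
- 1.4/3.19 = 0.44, as printed.

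Under that assumption both printed effect sizes, 0.44 and 0.35, fit a difference of 1.4 kg, and neither fits 1.3 kg.

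**The case against.** The strongest reply is that d may not be the wrong number. Step 5 shows that both effect sizes in the paragraph agree with a 1.4 kg difference if the pilot groups were equal. One pilot mean may simply be misprinted, in which case 85% power is right. This stands. It is not proof: unequal pilot groups could also produce 0.44, or the same slip could have been made twice. A reader might infer that the trial's true power is 80% and that the 85% is simply false. The document does not support that, because the 80% is conditional on the printed means.

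The other replies carry less weight.

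- *A d of 0.35 is a legitimate planning choice, and power at that value is as stated.* Both parts are true. But the section does not present 0.35 as a free choice. It gives a derivation, and the derivation yields a smaller effect.
- *Larger effects are likely at 6 months than at 3.* The section says so, then declines to size on that expectation.
- *The primary analysis is adjusted, so the t-test understates power.* This is possible. Covariates explaining about 11% of the outcome variance would restore 85% at 153 per group (about 14% at 148). The document gives no such figure, so this cannot be credited or ruled out.
- *Everyone is analysed, because missing weights are replaced by baseline (Statistical analyses).* This keeps 170 per group but adds zero changes. Assuming 10% carried forward in each arm, the difference becomes 0.9 × 1.3 = 1.17 kg. The arm variances are 0.9 × 16 + 0.09 × mean², giving a common SD of about 3.85 kg. Then d is about 0.30 and power at 170 per group is again about 80%.
- *340 has slack, since 296/0.9 = 329.* The 153-per-group row already includes it.

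**Conclusion.** The paragraph is wrong as written: its stated inputs give d = 0.325, not 0.35, and nothing elsewhere in the article reconciles them. The step from 0.35 to 148 per group is correct.

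If the printed means are right, power for 1.3 kg is 79.6% at 148 per group and 80.9% at 153, about 4 to 5 points below the stated 85%. This rests on a two-sided 0.05 unadjusted t-test with SD 4 kg in both groups. If a pilot mean is misprinted and the difference is 1.4 kg, the 85% holds. The document does not show which.

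A reader might also infer that the trial is underpowered or must enrol more. That does not follow. On the less favourable reading power is still about 80%, and the article's description of the trial as fully powered is tied to no numerical threshold. This is a should-fix correction to the power statement.

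**What to change.** Check the pilot means against the pilot data, then restate the paragraph in whichever form applies:

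1. If the difference is 1.3 kg: give d = 0.325 at SD 4 kg, with about 80% power at 148 per group and about 81% when 340 are randomised and 10% are lost.
2. If a pilot mean is misprinted: correct it so that the difference is 1.4 kg, and leave 0.35 and 85% as they are.
3. If 0.35 is to be kept as a planning choice: say that 148 per group gives 85% power for a 1.4 kg difference at SD 4 kg, and remove the claim that this follows from the printed pilot means.

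In each case the pilot d of 0.44 should be checked in the same pass. The cost is one paragraph, with enrolment and analysis unchanged. Under the first form the stated power becomes 4 to 5 points less favourable.

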### Recruiting and screening eligible participants

Participants will be recruited from the Tampa Bay area through flyers, word of mouth, and small media (e.g., websites, clinical trials advertisements) using culturally appropriate recruitment materials designed to engage Black women. Established relationships between Moffitt Cancer Center and the Tampa Bay Community Cancer Network will also be leveraged to aid in the recruitment of community volunteers for this research study. Recruitment campaigns will be conducted across Years 2-5 of the project to enroll approximately 85 participants per each of four waves, allowing for delivery of at least four treatment groups per cohort (two BWL-Stress and two BWL-Alone groups) with approximately 21 participants per group. Based on a conservative estimate of a 35% recruitment yield obtained from our preliminary research [24, 30], we anticipate pre-screening approximately 970 individuals (~ 323 per year) to enroll 340 participants over four waves. Method of recruitment will be documented.

Interested individuals will initially be screened by telephone by research staff. Based on preliminary eligibility, individuals will be scheduled for a baseline visit to confirm eligibility and complete the informed consent process. Eligible participants will complete all baseline assessments prior to randomization. The random allocation sequence will be generated with computer-generated random numbers.

### Intervention

Both treatment conditions will include a DPP-based lifestyle change curriculum presented in a group-based format in 26 sessions over a 1-year period. DPP is a structured lifestyle change program focused on reducing caloric intake and increasing physical activity to at least 150 min per week [31]. DPP employs evidence-based behavior change strategies such as self-monitoring and goal setting to promote lifestyle changes. Based on the original DPP study in which participants lost 5-7% of baseline body weight and the risk of developing diabetes was reduced by 58% in high-risk adults [31], as well as follow-up studies showing similar successes [32, 33], DPP has been adopted as a Centers for Disease Control (CDC)-recognized lifestyle change program. Consistent with the CDC-recommended meeting schedule, participants will meet once a week for 4 months (sessions 1 to 16), every other week for 2 months (sessions 17 to 20), and once a month for 6 months (sessions 21 to 26) [34]. Importantly, the two conditions will be equivalent in the format, frequency, and duration of contacts, and will differ only in the material that will supplement the DPP-based behavioral lifestyle change curriculum.

#### Community advisory board

A Community Advisory Board (CAB) consisting of five Black women from the Tampa Bay area contributed personal and professional opinions about stress management curriculum materials. CAB members included two consultants, a director/program manager, a nurse, and a public health manager. All CAB members had experience working in a leadership role in a community nonprofit or business. These women were selected to serve on the CAB primarily because of their community/health advocacy experience, their racial- and sex-concordance with the targeted population for the study, and because they represent different perspectives (e.g., race, sex, age, geography) that our research team wanted to ensure were reflected in the intervention materials. The CAB met for four weekly 1-h sessions, in which stress management session content, impact, and usability, as well as cultural relevance of wording and images, was discussed. Members were sent 6-7 session documents about 5 days prior to each meeting. Each stress management document was reviewed individually, and each CAB member was compensated $500 after all meetings were completed.

### BWL-stress

BWL-Stress will deliver the DPP-based lifestyle change curriculum during 26 60-min group sessions, each of which will also include an additional 20-min training session focused on introducing and reviewing stress management strategies (Table 1). The total session time will be approximately 80 min. Our pilot study demonstrated the feasibility of introducing stress management techniques within a 20-min training [24], and other studies have shown that 15-20-min bouts of focused breathing, mindfulness, and meditation can lead to documented reductions in stress indicators and improved cognition [35, 36]. Participants will be encouraged to apply the stress management strategies as frequently as needed outside of group meetings.

**Table 1 Tab1:** Curriculum for BWL-Stress and BWL-Alone during each study phase

DPP Lifestyle Change Curriculum	Women’s Health (BWL^**a**^-Alone)	Stress Focus (BWL-Stress)
**Weekly Sessions**		
Session 1: Welcome to DPP	Breast Self-care	Intro to Stress and Health
Session 2: Be a Fat and Calorie Detective	Skin Care	Identifying/Acknowledging Triggers of Stress
Session 3: Three Ways to Eat Less Fat and Fewer Calories	Dental Care	Meditation with Focus on Peace, Spirituality, Pride
Session 4: Healthy Eating	Heart Health	Benefits of Massage
Session 5: Move Those Muscles	Sleep Habits	Values Clarification
Session 6: Being Active – A Way of Life	Alcohol Use	Exercise as a Stress Reliever
Session 7: Tip the Calorie Balance	Tobacco Cessation	Progressive Muscle Relaxation
Session 8: Take Charge of What’s Around You	Domestic Violence	Navigating Misinformation and Finding Quality Resources for Your Needs
Session 9: Problem Solving	Age-Appropriate Cancer Screenings	Control What You Can, Accept What You Can’t
Session 10: Four Keys to Healthy Eating Out	Addictive Behaviors	Expressing Gratitude
Session 11: Talk Back to Negative Thoughts	Health Insurance	Developing an Action Plan with Achievable Goals
Session 12: The Slippery Slope of Lifestyle Change	Vaccines	Challenging dichotomous thinking
**Bi-Weekly Sessions**		
Session 13: Jump Start Your Activity Plan	Navigating Healthcare in the Digital Age	Financial Management
Session 14: Make Social Cues Work For You	Environmental Health	Setting Boundaries on Social Media
Session 15: You Can Manage Stress	Healthy Aging	Setting Boundaries by Learning to Say “No”
Session 16: Ways to Stay Motivated	Health Preparedness	Cognitive Restructuring
Session 17: Welcome to the Next Phase	Hair Care	Body Image and Self-Talk
Session 18: Food Preparation and Recipe Modification	Maternal Health and Menopause	Art as a Stress Reliever
Session 19: Healthy Eating – Taking It One Meal at a Time	Food Safety	Navigating Resources for Counseling and Therapy
Session 20: Healthy Eating with Variety and Balance	Breast Self-care and Mammograms	Self-Advocacy in Health Care
